**2.7 Statistical Analysis**

Descriptive statistics will be performed. Continuous variables will be controlled for normality by means of the Kolmogorov Smirnoff and Shapiro- Wilk tests. For normally distributed data, means and standard deviation (SD) will be calculated whereas median with interquartile range (iqr) or range will be used to summarize variables without normal distribution. Detection of significance between groups for these variables will be performed using the Student´s t-test or the Mann-Whitney test**.**

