**2.2.2. Secondary Objectives**

1. Evaluation of the frequency of adverse events, that is, failed localization and postoperative complications, with each method.

2. Time to specimen and total operative time for each technique.

3. The evaluation of healthcare personal experience with each technique via Likert scale items

4. Evaluation of patients’ QoL through PROs and their experience with each technique via PREMs questionnaires.

5. Cost-effectiveness analysis for each technique.

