**2.6 Sampling and Data Analysis Plan**

The sample size is calculated based on the principle of equivalence, allowing for the detection of a significant difference in resection ratios of 0.3 adjusted for a non-inferiority margin of 4% for re-excision rates and SLN detection. The literature suggests a resection ratio for the guidewire between 2-2.8. To obtain robust results, we lowered that to 1.8 and accepted a 1.5 resection ratio for the totally magnetic technique stemming from our previous pilot study ^25^. Two-sided p-value is set at 0.05 and power to 80%. An additional 10% to sample size calculation will be recruited as inflation to pragmatic settings and tolerance.

The participants will be randomized with an allocation ratio of 1:1 in blocks of 8. The R-Randomizer package will be used for the randomization. The allocated arms will be in dark envelopes, and neither of the involved disciplines will be able to know the arm in which the participants will be randomized beforehand. All participants will receive a code upon randomization consisting of the first three letters of the recruiting center and a number that will be consecutive. The data will be collected by appointed research coordinators.

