**3.2 Data collection**

The data collected included baseline patient and tumor characteristics, intraoperative details, and postoperative data including the pathology report, report of complications, and SPIO-induced skin staining.

Preoperative data:

- Age, Sex, BMI
- Radiographic tumour size and BIRADS (both mammogram and Ultrasound)
- Optimal resection volume
- Tumour location (side, quadrant, distance from nipple areola complex)
- Clinical size
- Preoperative core biopsy, needle size
- Histology, grade and receptor status
- Date of SPIO injection, US guided or not and volume
- Date of tumor localization, method employed, radiological guidance, time, and complications of the procedure.

Intraoperative data:

- Date of primary surgery
- Type of procedure
- Sentimag counts in breast and axilla after induction of anaesthesia
- Time from skin incision to specimen excision
- Radiologic margins (min, max)
- Skin excision information
- Sentimag counts on specimen and background
- Specimen weight
- Tracer or tracers that are used
- Successful SPIO SLNB
- Successful SLNB by any method
- Number of SLN
- Axillary procedure

Postoperatice data

- Date of pathology report
- Date answer was delivered to patient
- Specimen dimensions
- Histology and grade
- Size
- Receptor status
- Margin status and closest margin
- SLN number, number of metastases if any in SLN
- Skin staining and size
- Residual magnetic signal
- Planned reoperation
- Breast specific complications within 30 days, CD and CCI grading
- BREAST-Q preoperative, expectations, immediate postoperative, 6 months postoperative, 12 months postoperative

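### BREAST-Q is collected before surgery, but the only between-arm test stated for continuous variables makes no baseline adjustment, which costs precision on a secondary endpoint

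*Protocol*

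**What the plan says.** Quality of life is a secondary objective. Section 2.2.2 lists "Evaluation of patients’ QoL through PROs and their experience with each technique via PREMs questionnaires", and the Summary names it among the secondary endpoints. Section 3.2 gives the questionnaire schedule: "BREAST-Q preoperative, expectations, immediate postoperative, 6 months postoperative, 12 months postoperative". The instrument is therefore given once before the operation and three times after it, with expectations listed as a separate entry.

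Section 2.7 is a single paragraph on statistical analysis. It starts from continuous variables as a class: "Continuous variables will be controlled for normality by means of the Kolmogorov Smirnoff and Shapiro- Wilk tests". After saying how they will be summarised, it names the comparison: "Detection of significance between groups for these variables will be performed using the Student´s t-test or the Mann-Whitney test". BREAST-Q is neither named nor exempted. The protocol mentions no regression model, mixed model, baseline covariate or change score.

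**The concern.** A preoperative score on the same scale usually explains part of the spread in postoperative scores. A two-sample test on the postoperative scores leaves that spread in the error term, and any chance imbalance at baseline stays in the estimated difference. The data needed to remove both are already planned.

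The sample size in section 2.6 rests on the resection ratio, re-excision and sentinel node detection. Precision for quality of life is therefore whatever that sample happens to provide. At stake is a wider interval than necessary for BREAST-Q, and a null result that is harder to interpret.

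**Working it through.** **Is there a figure to reproduce?** No. The protocol gives no total N and no SD, effect size, power or correlation for BREAST-Q. Only relative precision can be worked out, over a range of assumed values.

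**Inputs**
- Allocation: "The participants will be randomized with an allocation ratio of 1:1 in blocks of 8" (section 2.6), so equal arms.
- Significance level: two-sided 0.05. Section 2.6 sets it for the sample size ("Two-sided p-value is set at 0.05 and power to 80" per cent); it is borrowed here for illustration.
- rho, the correlation between preoperative and postoperative score: assumed, 0.3 to 0.7.
- Equal variance before and after surgery: assumed.

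**Formulas** (variance of the arm difference relative to a t-test on follow-up scores, ignoring the one degree of freedom spent on the covariate)
- ANCOVA: 1 - rho^2
- t-test on change scores: 2(1 - rho)
- ANCOVA relative to change scores: (1 - rho^2) / [2(1 - rho)] = (1 + rho)/2
- Standard error of the follow-up t-test relative to ANCOVA: 1/sqrt(1 - rho^2)

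| Assumed rho | ANCOVA / follow-up | Change / follow-up | ANCOVA / change | Excess SE of follow-up t-test over ANCOVA |
|---|---|---|---|---|
| 0.3 | 1 - 0.09 = 0.91 | 1.40 | 0.65 | 5% |
| 0.5 | 1 - 0.25 = 0.75 | 1.00 | 0.75 | 15% |
| 0.7 | 1 - 0.49 = 0.51 | 0.60 | 0.85 | 40% |

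ANCOVA has the smallest variance in every row. Change scores do worse than follow-up scores alone below rho = 0.5, equal them at 0.5, and do better above it. These ratios are for the t-test. The Mann-Whitney test on follow-up scores also ignores the baseline, but the ratios are not exact for it.

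**Illustrative power.** Suppose the follow-up t-test had 80% power. The noncentrality is then 1.960 + 0.842 = 2.802.
- ANCOVA, Phi(2.802/sqrt(1 - rho^2) - 1.960): 0.836 at rho 0.3, 0.899 at 0.5, 0.975 at 0.7.
- Change scores, Phi(2.802/sqrt(2(1 - rho)) - 1.960): 0.658 at rho 0.3, 0.800 at 0.5, 0.951 at 0.7.

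The 80% starting point is itself an assumption, and the gain depends on it. With 20% unadjusted power the noncentrality is 1.960 - 0.842 = 1.118. At rho 0.5 this gives Phi(1.118/0.866 - 1.960) = Phi(-0.669), about 25%. At rho 0.3 the gain is about 1.5 points. With 10% unadjusted power and rho 0.5, power is about 12%. The variance ratios do not depend on this choice, so they are the figures to rely on.

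**The case against.** **The paragraph is generic.** Section 2.7 does not name BREAST-Q and does not say whether the tested variable is a raw score or a change. A reader might infer that the protocol prescribes discarding the baseline. The text does not go that far, because a two-sample test on change scores would comply with it. This stands, and the point is worded accordingly. It does not remove the loss, since change scores are less efficient than ANCOVA at every rho in the table.

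**This belongs in a SAP.** Covariates for a patient-reported secondary outcome are often left to that document, which is not at hand and may already contain an adjusted model. That is fair as far as silence goes. But section 2.7 is not silent: it names a test for continuous variables, and a better one is available from data already being collected.

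**The unadjusted test is valid.** A reader might infer bias. There is none under randomisation; chance imbalance adds noise, not systematic error. This stands in full and limits the weight of the point.

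**Section 4 does not raise the stakes.** It expects better patient comfort and satisfaction, and one might infer that this claim is at risk. The reasons given there are the protruding wire and the stress of the operation day. These concern experience of the localisation technique, which section 2.2.2 assigns to PREMs. Such experience has no preoperative counterpart, so baseline adjustment could not sharpen it.

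**The preoperative score may not be a true baseline.** Section 3.2 calls it only preoperative. The trial is open-label, and the Summary allows the marker to be placed up to 14 days before surgery but the wire at most one day before. The questionnaire could follow allocation or even marker placement, and adjusting for such a score could remove part of the effect. This stands and becomes a condition of the fix.

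**Conclusion.** The point holds as a loss of precision on a secondary endpoint. The stated two-sample tests either ignore the preoperative BREAST-Q score or, on change scores, use it less well than ANCOVA. Relative to a t-test on follow-up scores, ANCOVA would have 0.91, 0.75 or 0.51 of the variance at rho of 0.3, 0.5 or 0.7. At the low end the gain is slight.

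The result assumes equal variances at the two times and a rho that the protocol does not give. It also requires a preoperative score untouched by allocation. A headline such as power rising from 80% to 90% should not be read as a property of this trial: it needs both rho = 0.5 and an 80% starting power that nothing in the protocol supports. The primary endpoints are not affected. This is a worthwhile, inexpensive improvement, not a flaw that invalidates the comparison.

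**What to change.** Add to section 2.7, or settle in the SAP before outcome data are analysed:

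- For each BREAST-Q scale given both before and after surgery, estimate the between-arm difference with a 95% CI from a linear model of the postoperative score on randomised arm and preoperative score. Alternatively, use one mixed model over the three postoperative times with the same two covariates.
- Make this conditional on the preoperative questionnaire being completed before the allocation is known, and state that timing in section 3.2. Where that order is not met, do not use the score as the covariate.
- Keep the unadjusted test as a sensitivity analysis.
- Leave PREMs, and any scale without a preoperative counterpart, unadjusted.

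The cost is a few lines of text, with no new data, visits or patients. The small downsides are confirming when the preoperative score is obtained and stating how missing preoperative questionnaires are handled, for example by simple imputation of the baseline value.

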| Objectives | Primary:   - To examine how a magnetic marker compares to the guidewire in successful lesion localisation, minimal excess tissue removal and negative margins in surgery of non-palpable breast lesions. - To evaluate the combination of a ferromagnetic marker for tumour localisation with Superparamagnetic Iron Oxide Nanoparticle (SPIO) for sentinel lymph node detection (SLND) in early breast cancer treatment.   Secondary:   - To evaluate operative times and logistical efficacy of magnetic markers compared to guidewire in the above setting. - To evaluate patient as well as physician satisfaction with the use of this totally magnetic technique. - To evaluate patient quality of life (QoL) |
| Study Design and Methods | Multicentre Pragmatic Randomized Controlled Trial: Patients with confirmed non-palpable ductal cancer in situ (DCIS) or invasive breast cancer, planned for breast conserving surgery (BCS) and SLND will be randomized in two arms.  Arm 1: Lesion localisation with magnetic marker  Arm 2: Lesion localisation with guidewire  Axillary mapping will be done in both arms with the use of SPIO (1-1.5ml Magtrace ©, Endomag, Cambridge,UK) . In the interest of a pragmatic trial, lesion localisation with a magnetic marker as well as SPIO injection will be performed by either a breast surgeron or a radiologist and within a 14 day window before the operation according to local routines or case-per-case convenience. SPIO will be administered peritumoraly. Guidewire localisation will always be performed by a breast radiologist on the day or at most one day before surgery. All cases of localisation will be performed under local anesthetic.  The performing surgeon will document all relevant data in a case reporting form.  All patients will be followed up for postoperative complications, need for re-excision and QoL assessment for 2 years. QoL assessment will be done via PROs questionnaires and the patients experience will be evaluated with PREMs questionnaires.  All involved disciplines (surgeons, radiologists, co-ordinators) will rate their experience with each technique with Likert scale items. |
| Primary Endpoints | To examine the equivalence of magnetic marker and guidewire in successful localisation of non-palpable breast lesions by comparing:   - Re-excision rate - Resection ratio - Sentinel node detection rate |
| Secondary Endpoints | - Adverse events - Operative time - PROs and QoL evaluation - PREMs and cost- effectives analysis |

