| Statistical Analysis Plan | A pragmatic randomized open label study to investigate the equivalence of a magnetic marker localisation to guidewire localisation of non-palpable breast lesions. |
| Patient Population | Patients with biopsy confirmed non-palpable breast malignancies planned for BCS and SLND. |
| Study Duration | 5 years |
| Inclusion Criteria | -Patients aged ≥ 18 years  -Patients with ductal cancer in situ (DCIS) or invasive breast cancer (T1-T3) requiring  localisation planned for primary surgery including sentinel node  biopsy. |
| Exclusion Criteria | -Intolerance / hypersensitivity to iron or dextran compounds or  Sienna XP  -Patients with iron-overload disease.  -Patients with pacemakers or other implantable devices in the  chest-wall, or prosthesis in the shoulder.  -Patients deprived of liberty or under guardianship.  -Pregnant or lactating patients.  -Inability to provide informed consent. |

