**2.2 Objectives**

**2.2.1 Primary Objective**

1. The primary objective is a composite of the three components of successful breast conserving surgery for early breast cancer. These components include the re-excision rate, minimal excess tissue removal, and successful SLN detection. The aim of this trial is to compare these three variables between the two arms.

The hypotheses to be tested are:

1. Magnetic marker lesion localization is not equivalent to guidewire localization in terms of re-excision rates due to inadequate surgical margins. Adequate margins are considered “no tumour on ink” for invasive cancer and 2 mm for pure DCIS and will be assessed by specialized breast pathologists.

2. Magnetic marker lesion localization is not equivalent to guidewire localization in terms of excess tissue removal. This will be expressed as the resection ratio and will be assessed by the ratio of the Optimal Resection Ratio (ORV) to the Actual Resection Ratio (ARV).

- ORV will be calculated for each tumour based on the radiological dimensions of the tumor (in cases of discordance between different modalities, the largest dimension will be used) using the volume calculation formula for ellipsoid tumours
[figure not shown]
, where *r*1= x radius +1cm, *r*2=y radius+1cm, *r*3= y radius +1cm. In all dimensions, 1 cm is added as it is the universally accepted macroscopic margin for breast lesions^26^.

ARV will be calculated based on the specimen weight.

Optimally, the ratio $\frac{ARV}{ORV}$ should be as close to 1 as possible to ensure that no unnecessary tissue is removed which may jeopardize the cosmetic and functional outcomes of a breast conserving operation.

3. The combination of magnetic markers and SPIO is not equivalent to the combination of a guidewire and SPIO for SLN detection.

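### The protocol states equivalence for all three primary components, but sizes and tests the resection ratio for a difference and sets no equivalence margin for it

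*Protocol*

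**What the plan says.** - **Summary, Primary Endpoints.** The aim is "To examine the equivalence of magnetic marker and guidewire in successful localisation of non-palpable breast lesions by comparing" re-excision rate, resection ratio and sentinel node detection rate.
- **Summary, Statistical Analysis Plan row.** The trial is described as "A pragmatic randomized open label study to investigate the equivalence of a magnetic marker localisation to guidewire localisation of non-palpable breast lesions".
- **Section 2.2.1.** Three hypotheses are to be tested, each worded as non-equivalence: "Magnetic marker lesion localization is not equivalent to guidewire localization in terms of re-excision rates due to inadequate surgical margins"; "Magnetic marker lesion localization is not equivalent to guidewire localization in terms of excess tissue removal"; and "The combination of magnetic markers and SPIO is not equivalent to the combination of a guidewire and SPIO for SLN detection".
- **Section 2.6.** The sample size is said to rest on equivalence, yet it is described as "allowing for the detection of a significant difference in resection ratios of 0.3", from 1.8 with the guidewire to 1.5 with the magnetic technique. A non-inferiority margin of 4% is added for re-excision and node detection. The level is two-sided 0.05 and the power 80%.
- **Section 2.7.** After describing normality checks for continuous variables, it states: "Detection of significance between groups for these variables will be performed using the" Student's t-test or the Mann-Whitney test.

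**The concern.** Equivalence, non-inferiority and superiority differ in null hypothesis, in the need for a margin, and in the result that counts as success. The protocol uses all three without assigning one to each endpoint consistently. The conflict is sharpest for the resection ratio: its hypothesis is framed as equivalence, its sizing as detection of a difference, and its test as a difference test.

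At stake is what the primary result means. If the marker spares tissue as the planning values assume, Section 2.6 counts that as the finding the trial was built to make, while Section 2.2.1 had set out to show that the arms are alike. If the framework stays open, it could be settled after the data are seen, and the trial is open-label.

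**Working it through.** The protocol states no sample size, no standard deviation for the resection ratio and no expected re-excision or detection rate, so it has no figure to reproduce. The contradiction is shown by comparing sections. The arithmetic afterwards is illustration under assumed inputs.

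**1. Framework by endpoint**

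| Component | Summary and 2.2.1 | 2.6 | 2.7 |
|---|---|---|---|
| Resection ratio | equivalence | detect a difference of 0.3; no margin | t-test or Mann-Whitney |
| Re-excision | equivalence | non-inferiority, 4% | no test named |
| Node detection | equivalence | non-inferiority, 4% | no test named |

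No row is consistent across the columns. The sizing and test for the resection ratio agree with each other but not with the hypothesis. The binary rows have a one-sided margin under a two-sided aim.

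**2. Why a difference test cannot serve the resection-ratio hypothesis**

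Equivalence takes as its null that the absolute difference is at least some margin M, and rejects it when the whole confidence interval lies within −M to +M. The t-test takes as its null that the difference is zero, and Mann-Whitney that the distributions are the same. Rejecting that null shows a difference. Failing to reject it shows nothing about M. Neither outcome rejects non-equivalence, and the protocol gives no M for this endpoint.

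**3. Can any margin reconcile Section 2.2.1 with the planning values?**

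The planned difference is 1.8 − 1.5 = 0.3.

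- If M is 0.3 or less, the planning values lie outside or on the margin, so the arms are assumed not to be equivalent. With M exactly 0.3, two one-sided 5% tests would declare equivalence at most 5% of the time at any sample size.
- If M is above 0.3, equivalence is possible, but the difference on which the trial is sized has been declared unimportant.

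Either way the two sections do not describe one design.

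**4. Illustration: sample size depends on the framework**

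All figures use 80% power. The standard deviation and event rates are assumptions.

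- Detect 0.3 with SD 1.0, two-sided 0.05: n = 2 × (1.96 + 0.8416)² × 1.0² / 0.3² = 174.4, so 175 per arm. With SD from 0.6 to 1.5 the range is 63 to 393.
- Equivalence at ±0.3 with SD 1.0 and true difference 0: 191 per arm (each side 0.05) or 234 (each side 0.025).
- Non-inferiority at 4 points with equal event rates p, one-sided 0.025: n = 2p(1 − p) × (1.96 + 0.8416)² / 0.04². This gives 467, 883 and 1251 per arm for p = 5%, 10% and 15%.
- Equivalence at ±4 points, each side 0.025: 624, 1183 and 1675 per arm for the same rates.

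At 175 per arm, the 95% half-width for a risk difference is 1.96 × √(2p(1 − p)/175): 4.6 points at 5% and 6.3 points at 10%. At that size, an observed difference of zero would not exclude 4 points.

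**5. Illustration: why non-significance must not stand in for equivalence**

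Assume re-excision of 10% with the wire and 14% with the marker, exactly at the margin. Let SE = √((0.10 × 0.90 + 0.14 × 0.86)/n). Then P(non-significant) = Φ(1.96 − 0.04/SE) − Φ(−1.96 − 0.04/SE).

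| n per arm | SE | 0.04/SE | P(non-significant) |
|---|---|---|---|
| 175 | 0.0347 | 1.154 | 0.79 |
| 400 | 0.0229 | 1.744 | 0.585 |
| 883 | 0.0154 | 2.591 | 0.26 |

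A non-inferiority test at one-sided 0.025 would wrongly pass in about 2.5% of trials at each size. The protocol prescribes no difference test for re-excision, so the table describes a hazard to be excluded and not the written plan.

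**The case against.** The strongest reply is that Section 2.6 already contains a workable design. Superiority on one component with non-inferiority on the other two is legitimate, and a t-test or Mann-Whitney test suits the superiority part. On that view, equivalence is loose wording elsewhere. Much of this stands, and the repair adopts that split. It does not remove the contradiction: the hypotheses in Section 2.2.1 are presented as those to be tested, the Summary repeats the aim twice, and Section 2.6 itself invokes equivalence.

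A reader might also infer more than the protocol supports:

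- **That p > 0.05 will be taken as equivalence.** The protocol nowhere says so. It is a foreseeable misuse when an equivalence aim is paired with difference tests, not a stated rule.
- **That the Section 2.7 tests wrongly ignore the 4% margin.** Section 2.7 speaks of continuous variables, and the margin belongs to two binary endpoints. For those, the protocol names no test rather than a wrong one, and a statistical analysis plan may supply it. That absence is not part of this point.
- **That the trial has an 80% chance of finding non-equivalence on the resection ratio.** A difference can be statistically significant and still lie inside an equivalence margin. With no margin set, that probability is undefined.

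**Conclusion.** The contradiction is established from current protocol text and rests on no assumption. All three primary components are stated as equivalence questions. The resection ratio is sized and tested for a difference, with no equivalence margin. The other two carry a non-inferiority margin only. At the protocol's own planning values, success under Section 2.6 runs against the equivalence aim of Section 2.2.1.

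The size cannot be given as one figure. The sample sizes and re-excision percentages above rest on assumed standard deviations, event rates and arm sizes. They show that the choice of framework matters, not how this trial will perform. The point should be settled before analysis because it decides what each primary result allows the trial to conclude.

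**What to change.** Use one framework per endpoint, worded identically in the Summary and Sections 2.2.1, 2.6 and 2.7, following the split in Section 2.6:

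1. **Resection ratio:** superiority, reported as an effect estimate with a 95% confidence interval. If the sponsor wants equivalence instead, set and justify a margin and use two one-sided tests.
2. **Re-excision and node detection:** non-inferiority on the risk difference, marker minus wire, with a two-sided 95% confidence interval. Require an upper limit below +4 points for re-excision and a lower limit above −4 points for detection.
3. **Wording:** remove equivalence wherever no equivalence test is made, and state that a non-significant difference test supports no equivalence claim.
4. **Power:** state the sample size and its inputs, and restate the power for each endpoint under the chosen framework.

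Items 1 to 3 change wording and decision rules and need no new data items. It cannot be promised that patient numbers stay the same. With no sample size stated, item 4 may show that the non-inferiority comparisons need more patients than the resection ratio does. Under the assumptions above that is 467 to 1251 per arm against 175.
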